### Intervention

All participants will be instructed to maintain their extant therapy and daily exercise schedules, and they will be advised to drink sufficient water every day (2–3 L).

#### Positive control: canagliflozin group

Participants randomized into this group will receive canagliflozin for 3 months, which will be taken before breakfast (100 mg/day). Meanwhile, they will be asked to maintain their extant dietary habits.

#### LCD group

Participants randomized into this group will be required to reduce their intake of carbohydrates to less than 20% per day. No restriction will be required for the total caloric intake or the type and quantity of fat and protein. They will receive general educational materials on dietary advice and individual one-on-one consultations to meet their needs. Every participant will be asked to report their daily meals for the first 10 days after the intervention to obtain personalized instructions.

### Outcome measurements

#### Primary outcome

The change in HbA1c level is the primary outcome of this trial. It is defined as HbA1c after 3 months of treatment minus HbA1c at baseline.

#### Secondary outcomes

The secondary outcomes of this trial are the time in range and cost of antihyperglycemic agents. The time in range is defined as the proportion of time in the euglycemic range when using the FreeStyle Libre H Sensor (Abbott, England). Medications, including schedules and doses, at baseline and changes over 3 months will be recorded. The reduction or withdrawal of antihyperglycemic agents will be directed by an endocrinologist. The costs of the agents will be also recorded.

#### Exploratory outcomes

Physical examination and body composition test: heart rate, blood pressure, body mass index, and the waist-to-hip ratio will be recorded at each visit. Furthermore, body composition will be examined via bioelectrical impedance analysis (MC-780MA, Tanita, Japan).

Continuous glucose monitoring: The FreeStyle Libre H Sensor will be inserted by the same specialized operator at each center. The FreeStyle Libre H Sensor, accompanied by a reader, can provide glucose monitoring every 15 min for 14 days. Three days later, after the initial visit, participants in the LCD group will receive a FreeStyle Libre H Reader so that they can monitor their glucose levels and adjust their diet by themselves. They will be requested to provide their 24-h glucose levels to the researcher to obtain personalized diet instructions. The canagliflozin group will not get the reader and will be blinded to the monitoring results to avoid adjusting the meal or other behaviors, which may interfere with the results of the study. After a 3-month intervention, all participants will receive the sensor again, and they will be blinded to the monitor results to reduce interference with the final results.

Diet investigation and appetite scale: The dietary intake and appetite scale will be recorded at the initial visit and every month. Appetite, including hunger, fullness, and desire to eat, will be assessed using the 100 mm visual analog scale, with 0 (left) and 100 (right) representing the least and the most, respectively.

Blood test: At baseline, participants will eat a standard breakfast (542 kcal energy, 55% carbohydrate, 38% fat, and 7% protein) and undergo blood tests within 4 h. The specific items and time schedules of blood tests are listed in Table 1. At the final visit, participants in the canagliflozin group will consume a standard meal, and those in the LCD group will have an iso-caloric LCD meal (567 kcal energy, 10% carbohydrate, 79% fat, and 11% protein). Participants in both groups will repeat the tests performed at the initial visit. The LCD group will receive an additional visit with a standard meal to assess the urine glucose threshold. In addition, fasting glucose, insulin, C-peptide, β-hydroxybutyric acid, and 2-h postprandial glucose will be assessed at visits 1 and 2.

**Table 1 Tab1:** Items and schedule of blood tests

	Time(min)					
	0	30	60	120	180	240
Plasma glucose, insulin, and C-peptide	XX	XX	XX	XX	XX	XX
Free fatty acid and triglyceride	XX			XX		XX
β-Hydroxybutyric acid	XX			XX		XX
HDL-C, LDL-C, TC, apo A1, apo B, and apo E	X					
sd-LDL	X					
Electrolytes	X					
Renin–angiotensin–aldosterone system	X					

XX, baseline and final visits in the two groups and additional visits in the LCD group; X, baseline and final visits in the two groups

Ultrasound: At the initial and final visits, FibroScan and heart ultrasound will be performed to assess the degree of fatty liver disease and heart function.

Urine test: At the initial and final visits, the urinary albumin-creatinine ratio will be measured. Additionally, urine glucose, sodium, and potassium levels will be examined at 2 and 4 h after breakfast at these two visits. The renal threshold for glucose will be calculated according to previously published protocols [11, 12].

Safety: Hypoglycemia, ketoacidosis, and other adverse events will be recorded during the trial. Records include, but do not limit to, the relationship with the interventions, actions taken, and outcomes.

### Data collection and confidentiality

Researchers at each center will collect data according to the timeline schedule shown in Table 2. Researchers from each center will receive their own account to upload data and will be blinded to other centers.

**Table 2 Tab2:**
[figure not shown]
Participant schedule

During this trial, the privacy of all participants will be protected. Study documents, study reports, publications, and any other publicly published information will not include the participants’ names or other private information except as required by law. The collection, transmission, processing, and storage of participants’ information will comply with relevant laws and regulations to protect personal data from disclosure. Confidentiality of participants’ information will be strictly enforced by researchers. Confidentiality also covers information related to biological samples, in addition to the participants’ clinical information.

### Compliance and safety

For the canagliflozin group, the compliance of participants will be judged based on whether they take the drug according to the instructions and whether they add new treatment by themselves. For the LCD group, participants will be required to report the data of the FreeStyle Libre H Reader every day at the start of the intervention to ensure compliance with the diet. Furthermore, researchers will ask participants in the LCD group to report their whole-day diet randomly, about 4–5 times per month, and those in the canagliflozin group to report monthly.

All the adverse events occurring during the trial will be recorded. The records should include, but are not limited to, the time, signs, laboratory results, treatments, and outcomes. The relationship with adverse events will be determined by a clinician. Participants will be educated on how to handle emergency situations. For example, they need to have fast-acting carbohydrates when they have hypoglycemic symptoms and/or blood glucose levels lower than 3.9 mmol/L and report the situation to the researchers to get advice on adjusting their antihyperglycemic agents. The dose and frequency of canagliflozin are not allowed to be adjusted by the participants. If they do not tolerate or have adverse reactions, the researchers will be informed and decide the action according to the participant’s situation, such as drug interruption or withdrawal. When hypoglycemia occurs, the reduction order of antihyperglycemic agents is suggested to be from insulin injection and insulin secretagogues to other drugs.

### Data management and quality control

The Clinical Research Center of Shanghai Sixth People’s Hospital Affiliated to Shanghai Jiao Tong University School of Medicine (listed as Clinical Research Center below) will participate in center coordination, data audition, and the decision of study suspension and withdrawal due to serious adverse events. All data collected from participants will be entered into a database via a clinical trial management public platform (ResMan). The primary investigators of each center and statisticians have access to the final trial dataset. The study schedule will be reported to the Clinical Research Center and the Ethics Committee yearly.

Blood samples and data will be preserved for at least 5 years. All researchers involved in this trial will undertake adequate training before starting their work, and they are required to record detailed information and data truthfully.

The researchers will try their best to make all participants understand the purpose, benefits, and risks of the trial and provide a full and detailed explanation of the trial. If the participants have concerns, they can take the informed consent form home and consider it carefully or discuss it with their family members. The researchers will answer all the questions from the participants to ensure that they are fully informed about the entire trial.

The researchers of each center will discuss the protocol modifications, and the changes will be reviewed and approved by the Ethics Committees before implementation.

The participants will also be required to report their daily meals at the time points stated above. They will be requested to consume meals alone. When reporting, the net weight of food will be calculated using a kitchen scale, and the food will be photographed before and after eating with descriptions of the meal. If the food has a package, a weight and energy ratio will be also photographed. If the quality of the photos is poor or any information is absent, researchers will call back in a timely manner.

Concomitant medications prohibited during the study include glucocorticoid and other hyperglycemic agents.

### Statistical analysis

This study will analyze both the full analysis (FAS) set and per-protocol set and accept the non-inferiority hypothesis only if it is confirmed in both samples. Multiple imputations will be used to handle missing data in the FAS. To avoid potential bias in the results, which may be due to methodological decisions or our datasets, we will perform a sensitivity analysis. Subgroup analyses will be performed according to HbA1c levels, medication history, and diabetes duration. Statistical analysis will be performed using SPSS Ver.21.0 software. Data are presented as mean ± standard error or median (25th–75th percentiles) for continuous variables and as percentages (%) for categorical variables. Baseline and endpoint differences between groups will be analyzed using the independent *t*-test or Mann–Whitney *U* test for continuous variables and the chi-square test for categorical variables. Comparisons within each group (before and after the 3-month intervention) will be performed using a paired *t*-test or Wilcoxon test. Statistical significance will be set at *P* < 0.05. This study will not include interim analyses.

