## Methods/design

### Design

LoCaT is a multicenter, randomized, positive-controlled, parallel-group, and non-inferiority trial. Participants will be recruited from three academic hospitals in China: Shanghai Sixth People’s Hospital Affiliated to Shanghai Jiao tong University School of Medicine, Shanghai Eighth People's Hospital, and Ningbo First Hospital.

A total of 120 participants will be enrolled in the study. Competitive enrollment was used to recruit participants, with an allocation ratio of 1:1 for the canagliflozin and LCD groups. The participants will receive the intervention, and data will be collected. The report will be written according to Standard Protocol Items: Recommendations for Interventional Trials [6].

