### Sample size

This is a non-inferiority trial, and the primary outcome is the change in HbA1c from baseline (△HbA1c) to 13 weeks after treatment. According to previous studies and our pilot study, the standard deviation of △HbA1c was estimated as 0.73 for both groups [8–10]. Sample size was calculated using PASS software (version 11.0), with an alpha of 0.025 and beta of 0.2, and 54 samples per group were needed. Considering a 10% loss during follow-up, a total of 120 samples is reasonable for this study.

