### Recruitment, screening, and randomization

T2DM patients with poor blood glucose control will be recruited at three hospitals in Shanghai and Ningbo, China. First, clinical endocrinologists will introduce the purpose, risks, and benefits of the study to T2DM patients. Then, researchers will communicate with those interested in the trial and confirm whether they meet the inclusion and exclusion criteria. Finally, informed consent will be obtained, and the initial visit will start.

The table of random numbers will be generated by a statistician with particular random seeds. Variable block sizes of 4 and 6 will be used and stratified by whether HbA1c is between 7.5% and 8.5% or above 8.5% and whether the patients have taken antihyperglycemic agents in the past 3 months. Sealed envelopes containing group information will be prepared. The sequence number for each stratification will be typed on the surface of the envelope. The researchers will open the envelopes according to the sequence of enrollment and identify the group. Participants will be randomly assigned in a 1:1 ratio to the canagliflozin or LCD group. Each participant will have a unique study number.

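### The stated between-group test for HbA1c change is unadjusted, leaving unused the precision available from baseline HbA1c and prior medication, both stratification factors

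*Protocol article*

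**What the plan says.** All references are to the protocol article.

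- **Recruitment, screening, and randomization:** allocation is in blocks of 4 and 6, "stratified by whether HbA1c is between 7.5% and 8.5% or above 8.5% and whether the patients have taken antihyperglycemic agents" in the past 3 months.
- **Primary outcome:** the endpoint is the change in HbA1c. "It is defined as HbA1c after 3 months of treatment minus HbA1c at baseline".
- **Statistical analysis:** "Baseline and endpoint differences between groups will be analyzed using the independent" t-test or the Mann–Whitney U test for continuous variables. No ANCOVA, regression or stratified test is named anywhere. HbA1c level and medication history reappear only as subgroup factors. Non-inferiority must be confirmed in both the full analysis set and the per-protocol set. A sensitivity analysis is promised, but its content is not given.
- **Sample size:** "the standard deviation of △HbA1c was estimated as 0.73 for both groups", and the calculation was run "with an alpha of 0.025 and beta of 0.2, and 54 samples per group were needed". No non-inferiority margin or assumed true difference is given.

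**The concern.** The design treats baseline HbA1c and recent drug use as important enough to stratify on, but the stated comparison then makes no use of them as covariates. Stratified allocation balances the arms on these factors. If they predict the change in HbA1c, an unadjusted test still counts their variation as error, so its standard error is larger than it need be. Subtracting baseline does not cure this: a change score fixes the slope on baseline at 1 and leaves regression to the mean in place, and entry HbA1c may lie anywhere from 7.5% to 11%.

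Non-inferiority is judged on a confidence limit and has to hold twice. The Discussion itself expects that compliance with the diet may be poor, so the per-protocol set could be the smaller one, and there any spare precision is worth most.

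The choice between a t-test and a Mann–Whitney test is a further difficulty. The rank test, as named, does not supply an estimated mean difference with an interval, and that is what must be compared with a margin on mean change.

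**Working it through.** **Inputs from the document.** SD of change 0.73 in both groups; alpha 0.025; beta 0.2; 54 per group; 10% loss; 120 in total; 1:1 allocation.

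**Assumptions, because the document is silent.** Margin 0.40 HbA1c points and true difference 0, both back-solved below; alpha taken as one-sided; |rho|, the correlation between baseline HbA1c and its change, varied from 0 to 0.6.

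**1. The plan's own figure.** The normal formula is n = 2 × SD² × (1.960 + 0.842)² / margin².

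- At margin 0.40 it gives 53. The noncentral-t calculation gives exactly 54, with power 0.805.
- Solving the normal formula for the margin at n = 54 gives 0.73 × 2.802 × √(2/54) = 0.394.
- Margins of 0.35, 0.45 and 0.50 give 69, 42 and 34, so only about 0.39 to 0.40 fits with a true difference of 0.
- A two-sided alpha of 0.025 at margin 0.40 gives 64, so the one-sided reading fits.
- Loss: 54 / 0.9 = 60 per group, 120 in total, as stated.

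**2. Unadjusted interval.** Half-width = t(0.975, 106) × 0.73 × √(2/54) = 1.983 × 0.1405 = 0.279. This does not depend on the margin.

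**3. Adjusted interval and power.** Residual SD = 0.73 × √(1 − rho²). ANCOVA on treatment, baseline HbA1c and prior medication leaves 108 − 4 = 104 degrees of freedom. Half-width = t(0.975, 104) × residual SD × √(2/54). Power comes from the noncentral t with noncentrality 0.40 / (residual SD × √(2/54)). The last column is 54 / (1 − rho²), the number per arm that an unadjusted test would need for the same variance.

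| \|rho\| | Residual SD | 95% CI half-width | Power at margin 0.40 | 54 per arm is worth |
|---|---|---|---|---|
| Unadjusted | 0.730 | 0.279 | 0.81 | 54 |
| 0 | 0.730 | 0.279 | 0.81 | 54 |
| 0.2 | 0.715 | 0.273 | 0.82 | 56 |
| 0.3 | 0.696 | 0.266 | 0.84 | 59 |
| 0.5 | 0.632 | 0.241 | 0.90 | 72 |
| 0.6 | 0.584 | 0.223 | 0.94 | 84 |

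**4. Error rate under stratified allocation.** A simulation used 108 evaluable patients, stratified blocks of 4 and 6, and 3,000 runs per setting. Baseline HbA1c was truncated to 7.5–11%. Prior medication was assumed in 70% of patients, with no effect of its own on change. The adjusted model contained baseline HbA1c, prior medication and the HbA1c stratum. With the true difference set at the margin, the nominal one-sided error is 0.025, and the Monte Carlo standard error is √(0.025 × 0.975 / 3000) = 0.003.

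| rho | t-test error | Adjusted error | t-test power | Adjusted power |
|---|---|---|---|---|
| 0 | 0.020 | 0.019 | 0.81 | 0.80 |
| 0.3 | 0.025 | 0.028 | 0.81 | 0.84 |
| 0.5 | 0.015 | 0.023 | 0.82 | 0.90 |
| 0.6 | 0.015 | 0.023 | 0.82 | 0.94 |

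The unadjusted test never exceeds its nominal error and is conservative once baseline predicts change well. The adjusted test stays at nominal within simulation error.

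**The case against.** The strongest reply is that nothing here is invalid. An unadjusted comparison in a randomised trial is sound, and the sample size rests on the SD of raw change, which is the variance that such a comparison uses. Design and analysis agree. That stands, and it limits the point to efficiency.

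Four other replies deserve an answer.

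- **Baseline is not ignored.** It is subtracted in the endpoint, stratified on, and used for subgroups. This is correct. What is missing is its use as a covariate.
- **The sentence on tests is generic.** It covers all continuous variables and does not name the change score or the non-inferiority interval. Applying it to the primary outcome is an inference, though it is the only between-group method named for continuous variables. A full protocol or analysis plan may say more. The point concerns the method that the article names, not detail that it omits.
- **The size of the gain is unknown.** This is true. The article gives no correlation, and at |rho| = 0 there is no gain. Only the direction is secure.
- **Centre.** The Design section says "Competitive enrollment was used to recruit participants" at three hospitals, and centre is not a stratification factor. No centre effect is quantified, so adjusting for it is discretionary.

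A reader might infer that the trial falls short of its planned power, or that the unadjusted test risks a false claim of non-inferiority. The documents support neither. On the trial's own SD, and with the margin implied by its sample size, unadjusted power is 0.81, and the simulated error did not exceed nominal.

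**Conclusion.** The point holds as a missed gain in efficiency that should be taken up; it is not a flaw in validity. At 54 per arm, adjustment narrows the 95% CI half-width from 0.279 to 0.266 at |rho| = 0.3, 0.241 at 0.5 and 0.223 at 0.6, which is about 5%, 13% and 20%. It changes almost nothing at 0 to 0.2. Power would move from 0.81 to between 0.81 and 0.94 over the same range. The half-widths rest on the stated SD and the assumed correlation. The power figures rest also on the assumed margin of 0.40 and zero true difference.

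The Mann–Whitney alternative is a separate weakness that does not depend on any correlation: by itself it cannot deliver the estimate on which the non-inferiority decision is made.

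**What to change.** Make the primary non-inferiority estimate the adjusted mean difference, with its 95% CI, from an ANCOVA of HbA1c change on treatment, continuous baseline HbA1c and prior antihyperglycaemic use (yes/no). Fit the same model in the full analysis set and the per-protocol set. In the full analysis set, put the same variables and the treatment arm in the imputation model. Keep the unadjusted t-test as a sensitivity analysis, and do not use the Mann–Whitney test for the non-inferiority decision. Centre may be added as an optional covariate, provided that this too is decided in advance.

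The cost is small. The covariates are already collected for randomisation, SPSS fits the model, the sample size does not change, and the two covariates take two degrees of freedom (106 to 104; centre would take two more). It is still a change to a stated primary method. The Data management and quality control section requires ethics approval of protocol modifications, and Trial status expected recruitment to finish in December 2022. The change must therefore be documented, justified and fixed before any data are compared by arm.

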**Methods:**

This is a multicenter, randomized controlled trial. We will recruit 120 patients with poor-controlled T2DM. Participants will be randomly divided into canagliflozin and LCD groups in a 1:1 ratio. The primary outcome is the change in hemoglobin A1C levels after the 3-month intervention. The secondary outcomes are the time in range and cost of antihyperglycemic agents. Exploratory outcomes include physical examination, body composition, glucose variability, appetite, glycolipid metabolism, liver lipid content, and urine glucose threshold.

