Most T2DM patients may simultaneously have several components of metabolic syndrome, including obesity, hypertension, and hyperlipidemia [5]. Participants in this trial will undergo a tolerance test on a given diet at the beginning and end of the intervention, during which changes in insulin and C-peptide will be measured and islet function will be assessed. In addition, plasma lipids, especially fasting and postprandial free fatty acids and triglycerides, will be observed during treatment. LoCaT will also evaluate the body weight and composition and fatty liver disease of all participants, which may be improved after the intervention, and try to find out the intrinsic mechanisms of the effects of LCD on metabolic syndrome compared with those of canagliflozin.

A previous study showed that diabetes combined with hypertension significantly increased all-cause and cardiovascular mortality [18]. In addition, a meta-analysis found that for every 5 mmHg decrease in systolic blood pressure and 2 mmHg decrease in diastolic blood pressure, the risk of stroke in diabetic patients decreased by 13% and 11.5%, respectively [19]. In LoCaT, the blood pressure will be measured monthly to determine its changes, and the mechanism will be preliminarily explored through the assessment of body composition and the renin–angiotensin–aldosterone system.

A meta-analysis reported that both LCD and low-calorie diets decreased hunger in participants with obesity: a low-calorie diet favored increased satiety, whereas LCD favored decreased appetite; appetite suppression was attributed to ketosis (β-hydroxybutyrate ≥ 0.3 mmol/L) [20]. However, the study only evaluated fasting appetite at baseline and after intervention and did not evaluate postprandial appetite. In addition, canagliflozin has ketogenic effects, but there are few reports on its influence on appetite. This present trial will provide new insights into appetite before and after meals in the LCD group. The effects of canagliflozin on appetite will also be explored.

In conclusion, this study aims to determine whether LCD has the same effect as canagliflozin on glucose control in patients with T2DM, and the findings will provide new information on this topic.

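### Exploratory outcomes are measured between baseline and month 3, but no stated comparison uses those interim values and the between-group tests do not adjust for baseline (minor)

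*Protocol article*

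**What the plan says.** The collection schedule is in the protocol article under Exploratory outcomes. For the physical examination, "heart rate, blood pressure, body mass index, and the waist-to-hip ratio will be recorded at each visit". For diet and appetite, "The dietary intake and appetite scale will be recorded at the initial visit and every month". For the laboratory markers, in addition to the baseline and final tests, "fasting glucose, insulin, C-peptide, β-hydroxybutyric acid, and 2-h postprandial glucose will be assessed at visits 1 and 2". The Discussion gives a purpose for one of these: "In LoCaT, the blood pressure will be measured monthly to determine its changes".

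The Statistical analysis section gives the method for continuous variables: "Baseline and endpoint differences between groups will be analyzed using the independent" t-test or the Mann–Whitney U test, with a paired t-test or Wilcoxon test within each group over the 3 months. It does not limit this to HbA1c. It also plans multiple imputation in the full analysis set and a sensitivity analysis, and gives no model for either.

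The abstract gives the status of these measures: "Exploratory outcomes include physical examination, body composition, glucose variability, appetite, glycolipid metabolism, liver lipid content, and urine glucose threshold". The primary outcome is separate and needs two time points only: "It is defined as HbA1c after 3 months of treatment minus HbA1c at baseline".

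**The concern.** The design is longitudinal for several outcomes, while every named comparison uses two time points at most. The between-group test takes the endpoint alone (or, on another reading, the change). The within-group tests do not compare the arms. Two things follow.

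- No stated comparison uses a value recorded between baseline and month 3. For blood pressure, the stated reason for monthly measurement has no matching analysis.
- The between-group tests leave out the baseline value, which for measures such as BMI or blood pressure may be the strongest available predictor of the endpoint.

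What is at stake is precision on exploratory comparisons between the arms, and clarity about what the interim data are for. The validity of the trial's main conclusion is not in question.

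**Working it through.** **Plan's own figure.** The article gives no variance, correlation or power figure for these outcomes, so there is nothing to reproduce for them. Its sample size rests on change in HbA1c at 3 months: 54 / (1 − 0.10) = 60 per group, 120 in total. Nothing below alters it.

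**Inputs.**
- Time points: baseline, two interim visits and month 3 (Exploratory outcomes). That the interim visits fall at months 1 and 2 is presumed, because Table 2 is not shown.
- Correlation r between any two visits: not given. Assumed equal for all pairs, 0.4 to 0.7.
- Share missing month 3: 10%, taken from the loss to follow-up in the Sample size section.

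**Step 1: month-3 contrast, all participants observed.** Take the variance of one visit as 1.
- Unadjusted endpoint test: 1
- Change-score test: 2(1 − r)
- Baseline-adjusted month-3 contrast: 1 − r²
- Adjusted against endpoint: 1 − r²
- Adjusted against change score: (1 − r²) / [2(1 − r)] = (1 + r)/2

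| r | adjusted / endpoint | adjusted / change score |
|---|---|---|
| 0.4 | 0.84 | 0.70 |
| 0.5 | 0.75 | 0.75 |
| 0.6 | 0.64 | 0.80 |
| 0.7 | 0.51 | 0.85 |

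Against the endpoint test, the confidence interval shrinks by the square root: √0.84 = 0.92 and √0.51 = 0.71, so it is about 8% to 29% narrower. The r that matters here is the one between baseline and month 3. If correlation fades with time between visits, this gain is smaller.

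**Step 2: what the interim visits add at month 3.** With complete data and baseline-by-visit terms, they add nothing to the month-3 contrast beyond Step 1. If a share d misses month 3 only, the variance of the repeated-measures estimate relative to an analysis of completers is 1 − d·R², where R² is the share of month-3 variance explained by the two interim values once baseline is known. Worked case with equal correlation r = 0.5: the correlation between visits given baseline is r/(1 + r) = 1/3, R² = 2(1/3)² / (1 + 1/3) = 1/6, and the ratio is 1 − 0.10/6 = 0.983. Over r = 0.3 to 0.8, with equal correlation or with correlation that decays over time, the ratio runs from 0.991 to 0.949. That is a saving of about 1–5%.

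**Step 3: average over the three post-baseline visits.** Without baseline adjustment, its variance relative to one visit is (1 + 2r)/3: 0.60 at r = 0.4 and 0.80 at r = 0.7. With baseline adjustment on both sides, the ratio is [(1 + 2r)/3 − r²] / (1 − r²), which is 0.49 at r = 0.3 and 0.63 at r = 0.8. This is a larger gain, but for a different quantity: the mean arm difference over three visits, not the difference at month 3.

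**The case against.** The strongest reply is that this is a condensed article. A longitudinal model for exploratory outcomes is commonly left to the full protocol or analysis plan, neither of which is shown. An endpoint test on an exploratory outcome is valid, so a mixed model is a gain in efficiency and not the repair of an error. This largely stands and is why the point is minor. It does not remove the point, because the article is not silent: it names a method for continuous variables in general, and that method fits the described schedule poorly.

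Four stronger readings are tempting and are not supported.

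- **That the interim data are discarded.** No section says so. They could enter the multiple imputation, the sensitivity analysis, descriptive summaries, or the monitoring of safety and diet. The documents support only that they enter no stated comparison.
- **That everything is collected monthly.** This is explicit for blood pressure, diet and appetite only. The timing of the other measures depends on the participant schedule, which is not shown.
- **That the plan forgoes the equivalent of 25–67% more patients.** This comes from Step 3 (1/0.80 = 1.25 and 1/0.60 = 1.67). It sets a three-visit mean against a single visit, so it holds only if the arm difference is constant over the three months. The article gives no ground for that, and its Discussion warns that compliance with the diet may be poor.
- **That a participant who misses the last visit contributes nothing.** Imputation is planned in the full analysis set.

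**Conclusion.** The point holds in a limited form. The stated between-group comparisons ignore both the interim values and the baseline value for the exploratory outcomes. A baseline-adjusted month-3 contrast would have 0.84 to 0.51 times the variance of the stated endpoint test, or 0.70 to 0.85 times that of a change-score test, if r lies between 0.4 and 0.7 and is equal across visits. Both conditions are assumptions. Nearly all of the gain comes from baseline adjustment, with about 1–5% from the interim visits when 10% miss month 3. The primary HbA1c analysis and the sample size are unaffected. Severity: minor.

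**What to change.** For blood pressure, heart rate, BMI, waist-to-hip ratio, appetite and the fasting markers, replace the endpoint t-test or Mann–Whitney test with a mixed model for repeated measures. Its terms are arm, visit, arm-by-visit, baseline value and baseline-by-visit. Log-transform skewed variables such as insulin and β-hydroxybutyrate, since the model takes the place of the rank test there.

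Report the month-3 arm difference with a 95% CI as the main result. Report the average over the post-baseline visits beside it, labelled as a supplementary and different estimand. Settle this before the data are examined. If the sponsor prefers endpoint tests, the plan should at least say what the interim values are for and adjust the between-group comparison for baseline.

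The cost is slightly more analysis work, a check of the covariance structure and transformations, and effects on a ratio scale for the logged variables. No new data, visits or participants are needed, and the planned software can fit mixed models.
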